**Aim 3. Incremental CEA of alcohol use initiation prevented, and level of alcohol abuse deterred.**

We will test the hypotheses that a dual inoculation is cost-effective in deterring alcohol use outcomes relative to other experimental groups. Separate CEAs will be conducted for each different outcome including alcohol use initiation, use escalation, alcohol problems, and health-related quality of life from two perspectives: society and intervention provider. The time frame for the intervention is 5 or 7 weeks. The analytic horizon for the CEA, that is, the period over which costs and outcomes will be measured, is 4 years. Costs and outcomes will be converted to present-day values using a 3% discount rate, with 2%-10% used in a sensitivity analysis. Future costs and outcomes will be discounted back to the time when the intervention first occurred. The intent-to-treat analyses of intervention effects discussed in Aim 1 will be used for estimating outcome effects.

Best-practice guidelines prescribe calculating an incremental cost-effectiveness ratio (ICER) when comparing the cost-effectiveness of one approach (dual inoculation) with others (control, preadolescent inoculation, mid-adolescent inoculation). The ICER represents the incremental costs (from the aforementioned cost analysis) divided by the incremental effectiveness. The result is a measure of the net costs of the intervention for each one-unit gain in the outcome measure: for example, the cost per case of alcohol problems prevented.

Per best practice, we will account for uncertainty in the ICER with cost-effectiveness acceptability curves (CEACs), derived from the joint density of the individual-level costs and effects of the intervention of interest. A CEAC is generated by estimating net benefits of an intervention:

$$NB = \lambda(TotalHealthOutcomesPrevented_B - TotalHealthOutcomesPrevented_A) - [(InterventionCost_B - HealthCostAverted_B) - (InterventionCost_A - HealthCostAverted_A)]$$

The key features of NB are that it no longer includes a ratio, that one can calculate the  $p$  (NB > 0) at alternative values of  $\lambda$ , and that these values can be plotted, generating the cost-effectiveness acceptability curve. The CEAC thus represents the proportion of the density at which the intervention is cost-effective for a range of values of  $\lambda$ . The  $\lambda$ , which is unknown, represents the policy maker's varying degrees of tolerance for different resource allocation decisions, and the CEAC provides the necessary information for an informed decision under uncertainty. Because we do not know the threshold for  $\lambda$  below which decision makers would choose to implement the intervention based on the CEA result and above which they would choose not to implement, we will construct CEACs for varying levels of  $\lambda$ . To provide an additional level of sensitivity analysis, parametric estimation of the joint densities will be estimated indirectly via parametric bootstrapping and Monte Carlo simulation using the individual-level data. These methods allow for the uncertainty of the ICER to be represented on the cost-effectiveness plane along with a visual representation of the ICER confidence intervals.

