### Random assignment and contamination.

After pretest, families will be assigned randomly to one of four experimental groups: (a) *preadolescent inoculation*, (b) *mid-adolescent inoculation*, (c) *dual inoculation* control, and (d) control. Although the efficacy of SAAF and SAAF–Teen have been established, inclusion of a

control condition provides a baseline from which to compare normative alcohol use behavior in the population to both single- and dual-inoculation groups; it is also essential for comparing the single inoculations' economic efficiency. Preadolescent inoculation families will be assigned to receive SAAF at age 11 with no further intervention. Mid-adolescent inoculation families will receive SAAF–Teen at age 14. The dual-inoculation group will be assigned to receive both SAAF at age 11 and SAAF–Teen at age 14. The control condition involves no intervention contact. Participants will be notified if they are selected to participate in SAAF shortly after pretest. No participants will know if they are to receive SAAF–Teen until several months prior to its implementation. For each intervention implementation, families who are not attending a program receive written information by mail regarding adolescent development and alcohol use. Sending these materials is intended to maintain investment in the project for families who are not attending an intervention. No alcohol use effects are expected based on receiving written materials. All families will be followed across the course of the proposed study and assessed regardless of the number of intervention sessions they attend (intent-to-treat design). Information will be collected from family members about their participation in family enrichment programs offered in the school or community. The potential effects of participation in other programs (contamination) will be examined and statistically controlled in data analyses, as Lang et al. described.

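### Aim 3 gives two-strategy cost-effectiveness rules for a choice among four arms, so the plan does not yield each strategy's probability of being best or the single-programme comparisons

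*Combined protocol and SAP*

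**What the plan says.** The section on random assignment and contamination sets up four arms: SAAF at age 11 (preadolescent), SAAF-Teen at age 14 (mid-adolescent), both programmes (dual), and a control with no programme. It gives an economic reason for the control: "it is also essential for comparing the single inoculations' economic efficiency".

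Aim 3 states its hypothesis for one arm: "We will test the hypotheses that a dual inoculation is cost-effective in deterring alcohol use outcomes relative to other experimental groups". The ratio is defined "when comparing the cost-effectiveness of one approach (dual inoculation) with others (control, preadolescent inoculation, mid-adolescent inoculation"), so dual is always the index strategy. On uncertainty it says "A CEAC is generated by estimating net benefits of an intervention", followed by a formula in two strategies, B and A. The next paragraph evaluates p(NB > 0) over values of the threshold λ and concludes: "The CEAC thus represents the proportion of the density at which the intervention is cost-effective for a range of values of" λ. It presents the curve as what a decision maker needs under uncertainty.

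Aim 3 sets a 4-year analytic horizon, a 3% discount rate (2% to 10% in sensitivity analysis) and this time origin: "Future costs and outcomes will be discounted back to the time when the intervention first occurred".

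The documents do not rank the four arms by cost, remove dominated arms, choose among the contrasts, or define a four-way probability of being best. Aim 3 names no ratio of a single programme against control.

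**The concern.** A decision maker facing these four arms adopts one of them. The ratio that bears on adding the second programme compares dual with the next most costly arm that is not dominated. A ratio against control also credits dual with benefit that a single programme would deliver alone. Likewise, the probability that dual beats one comparator is not the probability that it is the best of four.

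Three things follow. If the contrasts point in different directions, nothing says which one governs the conclusion. The probability that each strategy is the best choice is not produced. And the comparison used to justify the control arm has no place in the analysis. The stake is the use made of Aim 3: a report could stress a favourable curve against control while a single programme is at least as good a choice, and still have followed the plan as written.

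**Working it through.** **The plan's own figure.** Five annual assessments give 5 − 1 = 4 yearly intervals, so Wave 1 to Wave 5 is 4 years. The stated horizon reproduces.

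**Assumed inputs.** The documents give no costs, effects or threshold.

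| Arm | Net cost | Cases prevented per person | Net benefit at λ = 30,000 |
|---|---|---|---|
| Control | 0 | 0 | 0 |
| SAAF-Teen | 800 | .08 | 2,400 − 800 = 1,600 |
| SAAF | 1,000 | .10 | 3,000 − 1,000 = 2,000 |
| Dual | 1,800 | .12 | 3,600 − 1,800 = 1,800 |

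The standard error of each arm's effect is taken as .045, with arms independent, effects normal and costs fixed. That fits the plan's 100 to 115 families per arm: for a risk of .30 to .40, √(.30×.70/115) = .043 and √(.40×.60/100) = .049.

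**Ratios under the written rule**
- Dual vs control: 1,800/.12 = 15,000.
- Dual vs SAAF-Teen: 1,000/.04 = 25,000.
- Dual vs SAAF: 800/.02 = 40,000.

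At λ = 30,000 dual passes two contrasts and fails the third, and no rule says which one decides. In sequence, SAAF-Teen vs control is 800/.08 = 10,000, SAAF vs SAAF-Teen is 200/.02 = 10,000, and dual vs SAAF is 40,000. The sequence leads to SAAF, which also has the highest net benefit.

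**Pairwise probabilities.** p(NB > 0) = Φ(ΔNB / (λ × SE × √2)), with denominator 30,000 × .045 × 1.414 = 1,909.
- Control: Φ(1,800/1,909) = .83.
- SAAF-Teen: Φ(200/1,909) = .54.
- SAAF: Φ(−200/1,909) = .46.

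**Best of four.** In 1,000,000 draws of the four effects, the share in which each arm has the highest net benefit is .04 for control, .26 for SAAF-Teen, .38 for SAAF and .32 for dual. The three pairwise values cannot recover the .32. They only bound it: at most the smallest, .46, and at least 1 − (.17 + .46 + .54) = −.17, that is, 0.

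**Range.** At λ = 30,000, halving or doubling precision is not needed to see the pattern. With SE .03, dual vs control is Φ(1,800/1,273) = .92, with best of four .32 for dual and .43 for SAAF. With SE .06 it is Φ(1,800/2,546) = .76, with .31 and .36.

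A second assumed set has costs 0/1,000/1,000/2,000 and control risk .40 reduced by 0/.05/.08/.10 for control/SAAF-Teen/SAAF/dual, with n = 100 per arm:

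| λ | Dual vs control | Dual vs SAAF | Dual best of four | SAAF best of four |
|---|---|---|---|---|
| 20,000 | .47 | .30 | .17 | .44 |
| 30,000 | .70 | .41 | .28 | .44 |
| 50,000 | .80 | .47 | .36 | .41 |
| 100,000 | .87 | .54 | .44 | .37 |

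The gap between the control contrast and the best-of-four probability persists throughout. Which arm leads depends on λ.

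**Discount origin.** The first programme falls at age 11 in the preadolescent and dual arms, at age 14 in the mid-adolescent arm, and never in control. If each arm used its own date, a SAAF-Teen cost would have weight 1.000 in the mid-adolescent arm and 1.03⁻³ = .915 in the dual arm (1.10⁻³ = .751 at 10%). A Wave 5 outcome is about 10 months after SAAF-Teen and 4 − .25 = 3.75 years after SAAF, so its weights would be .976 against .895 at 3%, and .924 against .699 at 10%. With one common date, weights for the same calendar time are equal in all arms.

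**The case against.** The plan names all three comparators for dual, so the decisive contrast is already there: the 40,000 above is a planned output. At point estimates, dual is best exactly when it beats each other arm, and the three differences from dual even fix the full ranking by subtraction. The planned .46 against SAAF already warns that dual is not favoured. The stated hypothesis concerns dual relative to the other groups, and pairwise curves fit it.

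Most of this stands. A reader might infer that the plan overlooks dual versus the next-best arm, or judges dual against control alone; the text supports neither. Nor does .32 show dual to be a poor choice, since the leading arm reaches only .38. What the objection leaves open is the missing decision rule, the probability that each strategy is best, which separate pairwise curves do not supply, and the single-programme comparisons promised elsewhere in the protocol.

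A reader might also infer that costs are discounted from a different date in each arm. The documents do not say so. That reading would leave control without an origin although control enters the contrasts, and the single 4-year horizon matches Wave 1 to Wave 5, whereas only about 10 months follow SAAF-Teen. A common origin is the more natural reading.

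**Conclusion.** The point holds as a gap in specification. Aim 3's ratio, net-benefit and acceptability-curve rules are two-strategy rules with dual as the index, and they do not complete a four-way decision analysis or deliver the single-programme comparisons. This follows from the text and needs no assumption.

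The size is illustrative only. On the first assumed set, .83 against control sits beside .32 for best of four, and the second set gives .70 beside .28 at the same threshold. Real costs and effects could widen or close that gap. The harm is moderate, because the contrast with the next-best arm will be reported.

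The discounting sentence is a minor ambiguity and not an error: it names no trial-wide date, though a common one appears intended. The unequal weights shown would arise only under the arm-specific reading.

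**What to change.** In Aim 3, add the following:

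1. Rank the four arms by mean cost, remove dominated and extendedly dominated arms, and report sequential ratios. State that these govern the choice among strategies. The single-programme comparisons, including those with control, then come into the analysis.
2. In each bootstrap replicate already planned, compute net benefit for all four arms. Plot each arm's probability of having the highest net benefit over λ, with the acceptability frontier.
3. Keep the pairwise dual contrasts as the test of the stated hypothesis.
4. As a clarification, state that costs and outcomes in all four arms are discounted to one common date, for example Wave 1.

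The cost is a change of wording and slightly more analysis and reporting. No new data are needed, the planned bootstrap output is reused, and the design is unchanged.
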